#### Data collection tools

Data will be collected using a self-report 21-item Depression Anxiety Stress Scale (DASS-21) and a revised version of the Fertility Adjustment Scale (R-FAS) [20]. Each of the DASS-21 subscales contains seven items on a 4-point Likert scale (0–3) from 0 (not at all true for me), 1 (to some extent true for me), 2 (considerably true for me), to 3 (absolutely true for me). A higher score indicates greater depression, anxiety, and stress.

Adjustment to infertility will be assessed using the self-report R-FAS, including 12 items on a 6-point Likert scale (1–6) from 1 (strongly disagree) to 6 (strongly agree). The final score will be obtained by summing the scores of questions; a higher score indicates a lower adjustment toward infertility.

To promote participant retention and complete follow-up, prior to each counseling session, the researcher will encourage couples who discontinue or deviate from intervention protocol to participate in counseling sessions through a telephone call. Missed data will be completed by the researcher through a telephone call and questions. Data monitoring in all phases will be done by the principal investigator.

#### Confidentiality

Researchers directly will be accountable for relevant information about the trial to the potential participants. When entering data in the datasheet, participants’ details will be removed, and the code will be assigned.

#### Data management and analysis

Data will be analyzed using the SPSS 19 software and statistical tests, including the independent *t*-test, pair *t*-test, chi-square, and repeated measures analysis of variance (RM ANOVA). If the measurements at the enrollment phase appear differently in the groups, analysis of covariance (ANCOVA), controlling for baseline data and independent variables (group as a fixed parameter and enrollment mean scores as a covariate), will be used. Also, the baseline value of outcome variables and potential confounding variables which are different between the two groups will be adjusted to avoid potential risk of bias and detect independent results. The data normality will be evaluated through the Kolmogorov-Smirnov test. If the data are not normally distributed, nonparametric tests such as Wilcoxon will be used. In the case of missing data, we will utilize the last value carried forward method to impute missing values.

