### Third phase: a randomized field trial study

#### Participants and setting

This parallel-group, double-blind, controlled, randomized field trial, superiority framework with an allocation ratio of 1:1 will be conducted on infertile couples who underwent infertility treatment in Isfahan Fertility and Infertility Center, Isfahan, Iran. Couples, at least one of whom suffers from mild to moderate depression, will be invited to participate in the quasi-experimental study. The inclusion criteria will include no history of severe mental disorders and no stressful event during the last 3 months. The exclusion criteria will be a stressful event or the onset of assisted reproductive treatment during the intervention and ovarian hyper-stimulation syndrome due to ovarian induction.

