#### Sample size

The sample size will be calculated for a 1:1 allocation ratio, considering presumed depression score reduction after the intervention, estimated sample loss, and 95% confidence level.

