#### Outcomes

The outcome will be the mean score of depression, anxiety, stress, and infertility adjustment and the magnitude of their change on enrollment and 3 months after starting the intervention in couples in the intervention group compared with those in another educational intervention (as the control group).

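### Baseline adjustment hinges on an undefined enrolment difference and further covariates are picked by observed imbalance, so most of the precision gain is forgone and the data choose the model

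*Protocol article*

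**What the plan says.** The Data management and analysis section of the third phase lists "statistical tests, including the independent *t*-test, pair *t*-test, chi-square, and repeated measures analysis of variance (RM ANOVA") as its tests. ANCOVA follows as a conditional step: "If the measurements at the enrollment phase appear differently in the groups, analysis of covariance (ANCOVA), controlling for baseline data". Its model has group as the fixed factor and the enrolment score as covariate.

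The next sentence says that the baseline value of the outcome variables will be adjusted for, together with further covariates: "potential confounding variables which are different between the two groups will be adjusted to avoid potential risk of bias". No covariate is named, and no test, threshold or size of difference defines when the arms differ.

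Two other places bear on this. The third-phase Participants and setting section describes a "randomized field trial, superiority framework with an allocation ratio of 1:1". The Outcomes section defines the outcome as "the mean score of depression, anxiety, stress, and infertility adjustment and the magnitude of their change on enrollment and 3 months" after the start of the intervention, compared with the control group.

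**The concern.** If allocation is sound, any enrolment difference between randomised arms is chance. Adjusting for the enrolment score is worthwhile because that score predicts the later one, and this holds equally in balanced and unbalanced samples. A rule that waits for a visible imbalance therefore leaves the adjustment out of most trials in which it would help.

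The trigger is also a matter of judgement. Whether scores look different, and which other variables count as different, is settled after the data are in hand. The model, and so the p-value, then depends on choices that nobody fixed in advance.

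The two adjustment sentences do not agree either. The first makes adjustment for the enrolment score conditional. The second can be read as always adjusting for baseline outcomes, with the condition limiting only the confounders. Two analysts could follow this section in good faith and fit different models.

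**Working it through.** **Inputs from the protocol.** 1:1 randomisation and superiority (Participants and setting); 95% confidence level (Sample size), taken as two-sided alpha 0.05 because sidedness is not stated; tests and trigger as above. The protocol gives no sample size, power, effect size, SD or baseline-outcome correlation, so it has no figure to reproduce.

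**Assumptions.** Correlation rho 0.3 to 0.7; standardised effect d = 0.5; 80% power; equal variance at both times; independent observations (pairing of partners ignored).

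**Sample size.** With the post-score SD set to 1, the variance entering the comparison is:
- post-score t-test: 1
- change score, equivalent to the group-by-time test in RM ANOVA with two time points: 2(1 − rho)
- ANCOVA: 1 − rho²

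Relative to ANCOVA, the post-score t-test needs 1/(1 − rho²) times as many observations. The change score needs 2(1 − rho)/(1 − rho²) = 2/(1 + rho) times as many.

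Per arm, n = 2 × (1.960 + 0.842)² × variance / d², which is about 62.8 × variance, rounded up.

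| rho | n: post score | n: change | n: ANCOVA | 1/(1 − rho²) | 2/(1 + rho) |
|---|---|---|---|---|---|
| 0.3 | 63 | 88 | 58 | 1.10 | 1.54 |
| 0.5 | 63 | 63 | 48 | 1.33 | 1.33 |
| 0.7 | 63 | 38 | 33 | 1.96 | 1.18 |

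**Power of the conditional rule.** This was simulated with 63 per arm and 100,000 trials per setting. The rule was taken as ANCOVA if a baseline t-test gives p<0.05, and otherwise the default test. ANCOVA was then used in about 5% of trials.

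| rho | Default test | Default alone | Conditional rule | Always ANCOVA | Loss (points) |
|---|---|---|---|---|---|
| 0.3 | post score | 79.2% | 79.5% | 82.7% | 3.2 |
| 0.3 | change | 65.2% | 66.4% | 82.8% | 16.4 |
| 0.5 | post score | 79.4% | 80.4% | 89.2% | 8.8 |
| 0.5 | change | 79.5% | 80.5% | 89.3% | 8.8 |
| 0.7 | post score | 79.7% | 81.7% | 97.3% | 15.6 |
| 0.7 | change | 94.9% | 95.3% | 97.3% | 2.0 |

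The share of ANCOVA's gain that the rule keeps is (conditional − default)/(ANCOVA − default). From the unrounded results it runs from 1.24/17.61 = 7% (rho 0.3, change) to 0.43/2.42 = 18% (rho 0.7, change).

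**Type I error, same simulation with no effect.** Applied mechanically, the rule rejects in 3.6% to 4.8% of trials. If the analyst may report the smaller of the ANCOVA and default p-values, rejection rises to 6.4% to 8.3%.

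**Conditional type I error of the post-score test.** Given a baseline difference of z, the test statistic is distributed N(rho × z, 1 − rho²), and it rejects beyond ±1.96. For rho 0.5 and 0.6:
- z = 0: 2.4% and 1.4%
- z = 1.5: 8.2% and 9.3%
- z = 1.9: 12.2% and 15.3%
- averaged over |z| < 1.96: about 4.3% and 4.0%

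**The case against.** The strongest reply is that the enrolment score is not ignored when ANCOVA is not triggered. RM ANOVA is among the listed tests and the outcome definition includes change, and both use the enrolment value. This stands in part. Against a change score the sample-size ratio falls as the correlation rises, and at rho 0.7 the power loss is only about 2 points. The ratio of 1.96 applies only to a post-score t-test. The change score is still less efficient than ANCOVA at every correlation examined. The section also does not say which of its listed tests decides.

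A second reply is that the rule does no harm to error control. For a fixed p<0.05 trigger this is right. A reader might infer inflation from the conditional rates at z = 1.5 or 1.9, but those are offset by rates well under 5% when the arms are well balanced, and the average over samples passing the check is below 5%. The protocol names no such test in any case.

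Third, a reader might infer from the paired t-test that within-arm improvement will be taken as proof of superiority, or that regression to the mean in couples selected for depression biases the result. The protocol supports neither. It only lists the paired test, and the Sampling and data collection and Outcomes sections describe between-group comparison. Both arms are selected in the same way, so regression to the mean is expected equally in each and does not bias the randomised contrast.

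Finally, a separate analysis plan might settle the matter. But this is a rule that the article states, not a detail that it leaves open.

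**Conclusion.** The point holds in a limited form. The section ties baseline adjustment to an undefined observed difference, selects other covariates by imbalance, and contains two sentences that can be read against each other. It would be too strong to say flatly that baseline outcomes are adjusted for only when the arms differ, because the second sentence leaves room for the other reading.

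The main cost is precision. For rho 0.3 to 0.7, the sample-size factor is 1.10 to 1.96 against a post-score test and 1.54 to 1.18 against a change score. With 63 per arm, d = 0.5 and a p<0.05 trigger, the power loss is about 2 to 16 points. These sizes rest on assumed inputs, on independent observations and on a two-time-point change analysis. A looser trigger would bring ANCOVA in more often and lose less.

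Overall type I error is not inflated by a mechanical p<0.05 rule. The risk of 6.4% to 8.3% depends on an analyst using the vague trigger to choose the better result. The protocol does not say that this will happen, but it does not prevent it. The plan should be changed, although the fault does not invalidate the trial.

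**What to change.** Replace the two adjustment sentences with one rule:
- ANCOVA, or an equivalent model with the enrolment score of the same scale as covariate, is the between-arm analysis for every outcome, whatever the observed balance.
- Any further prognostic covariates are named in advance. Selection by observed difference is dropped.
- The superiority conclusion rests on the between-arm contrast. Within-arm change is reported descriptively.

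The cost is analysis wording only, provided that it is done before outcome data are seen. The Recruitment section already has all four measures taken at the first interview, and the Outcomes section refers to enrolment scores, so no new data are needed.

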#### Sampling and data collection

After determining the eligible couples, X couples will be randomly selected by the researcher. To randomly assign the couples to the intervention and control groups, X closed envelopes containing blue and green cards will be prepared. The couples will be referred to the midwife consultant and receive one of the envelopes and complete demographic characteristics.

The midwife and participants will be blinded to the study group. After random allocation, one researcher, who will not be involved in sampling and random allocation, will assign each group’s card color. Couples’ depression, anxiety, stress, and infertility adjustment levels will be evaluated using valid questionnaires 2 and 3 months after starting the intervention and compared between the groups (Table 1).

**Table 1 Tab1:** Schedule for data collection during the trial

Time point	Study period				
	Enrollment	Allocation	Post allocation		Closeout
	Pre-baseline	Baseline	Time 1	Time 2	
Enrollment					
Eligibility screen	X				
Informed consent	X				
Allocation		X			
Participant characteristics					
Demographics		X			
Infertility profile		X			
Interventions					
Couple-based coping strategies		X			
Solution-oriented counseling		X			
Outcomes assessment					
Depression			X	X	X
Anxiety			X	X	X
Stress			X	X	X
Infertility adjustment			X	X	X

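### Covariates other than the enrolment score are adjusted for only if the randomised arms are seen to differ on them, which makes the model data-dependent and gives up precision

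*Protocol article*

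**What the plan says.** The trial is described under Participants and setting (third phase) as a "randomized field trial, superiority framework with an allocation ratio of 1:1". Under Sampling and data collection, allocation is by envelope: "X closed envelopes containing blue and green cards will be prepared". No stratification factor is mentioned. At that contact couples "receive one of the envelopes and complete demographic characteristics", and Table 1 lists demographics and an infertility profile at baseline without itemising either.

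The third-phase Data management and analysis section has two conditional rules. One concerns the outcome scores at enrolment: "If the measurements at the enrollment phase appear differently in the groups, analysis of covariance (ANCOVA), controlling for baseline data and independent variables". The other extends to further covariates: "potential confounding variables which are different between the two groups will be adjusted to avoid potential risk of bias". This point is about the second. The section names no covariate, gives no threshold for a difference, and lists no variable to be adjusted for regardless of balance. If nothing is judged to differ, the listed *t*-tests, chi-square test and repeated measures analysis of variance stand unadjusted.

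**The concern.** In a soundly randomised trial, baseline differences between arms are chance. What a covariate contributes to the analysis depends on how well it predicts the outcome, but this rule admits it according to how unequal it happens to be. Three consequences follow.

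- The model is known only after the arms have been compared at baseline, so it cannot be fixed in advance.
- With no definition of a difference, and four outcomes that nothing ties to a single covariate set, the analyst has room to choose.
- A variable that predicts the outcome but is balanced is left out, although including it would narrow the interval.

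Partner sex shows the last of these. The Background says men and women may carry the burden of infertility unequally. Couples are allocated as units, so if both partners' scores are analysed, each couple gives one woman and one man. Sex is then balanced between arms apart from dropout, and the rule would almost never select it.

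**Working it through.** The article gives no sample size (it says that "After determining the eligible couples, X couples will be randomly selected by the researcher"), no power, no standard deviation and no covariate count. There is therefore no figure of the plan's own to reproduce, and what follows is illustration.

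**Inputs from the article:** 1:1 randomisation; continuous outcome scores; a 95% confidence level, stated for the sample size.

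**Assumptions, not from the article:** different means two-sided p<0.05; independent baseline variables; 30 or 60 independent observations per arm; correlation ρ between covariate and outcome of 0.3, 0.5 or 0.7; a treatment effect giving about 80% power without adjustment.

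**Step 1: how often chance shapes the model.** For K independent variables the chance that at least one is flagged is 1 − 0.95^K.

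| K | Calculation | Chance |
|---|---|---|
| 1 | 1 − 0.950 | 5% |
| 5 | 1 − 0.774 | 23% |
| 10 | 1 − 0.599 | 40% |
| 20 | 1 − 0.358 | 64% |

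This measures how often the covariate set is chosen by chance. It does not measure harm.

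**Step 2: what always adjusting would gain.** One fixed covariate reduces the residual variance to 1 − ρ². An effect with 80% unadjusted power has a standardised size of 2.80 (1.96 + 0.84), so adjusted power is about Φ(2.80/√(1 − ρ²) − 1.96).

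- ρ = 0.3: variance factor 0.91, power about 84%
- ρ = 0.5: variance factor 0.75, power about 90%
- ρ = 0.7: variance factor 0.51, power about 98%

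**Step 3: simulation of the rule itself.** There were 8,000 runs under no effect and 4,000 with an effect. Results for one covariate and 60 per arm:

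| ρ | Quantity | Unadjusted | Adjust if p<0.05 | Always adjust |
|---|---|---|---|---|
| 0.3 | Power | 79.8% | 80.4% | 83.3% |
| 0.5 | Power | 78.3% | 79.5% | 89.0% |
| 0.7 | Power | 78.6% | 80.5% | 97.6% |
| 0.3 | Type I error | 0.046 | 0.045 | 0.049 |
| 0.5 | Type I error | 0.048 | 0.041 | 0.049 |
| 0.7 | Type I error | 0.049 | 0.035 | 0.045 |

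Simulation error is about √(0.05 × 0.95/8000) = 0.0024 for type I error and √(0.8 × 0.2/4000) = 0.006 for power.

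At ρ = 0.5 the rule gains 79.5 − 78.3 = 1.2 points of the 89.0 − 78.3 = 10.7 points available, about a ninth. The standard deviation of the estimated effect is 0.182 unadjusted, 0.175 under the rule and 0.159 always adjusted. The rule thus captures 0.007 of a possible 0.023, a little under a third.

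The conservatism has a simple source. The unadjusted analysis is kept only when the covariate is reasonably balanced, yet its standard error still allows for the larger imbalances that were screened out.

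At 30 per arm with one covariate, always adjusting gives 81%, 87% and 97% power at the three correlations. When ρ = 0.3 is spread over five covariates at 30 per arm, it gains nothing useful (77.8% to 78.0%), which argues for a short list.

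**The case against.** Four arguments can be made for the plan.

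1. **The rule is narrower than selection on imbalance alone.** It covers potential confounders, and a confounder must relate to the outcome, so variables that are merely noise seem meant to be excluded. This stands as a reading of the wording. It does not bring in balanced predictors, and it leaves both terms to be judged once the data are seen.

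2. **Detail may be left to a fuller document.** A variable list and a threshold could well sit in an analysis plan that is not shown. But the article does more than leave the list open. It fixes selection by observed difference, and a plan that followed it would inherit the fault.

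3. **The rule is not worse than no adjustment.** In the simulation it is slightly better on power and on the spread of the estimate, and adjusting for an imbalanced predictor does reduce error in that sample. This stands. The loss is relative to a fixed covariate set.

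4. **Large gains are not established for these covariates.** Nothing in the article supports a correlation of 0.5 or more for demographic or infertility variables, least of all beyond the enrolment score. This also stands. At 0.3 the gain is only a few points.

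A reader might go further and infer that the rule biases the result or inflates the type I error. The documents do not support that, and the simulated test was conservative. Inflation would need loose or repeated model choice, which the undefined criterion permits but which has not been shown. Nor can one infer that about half of such trials would report a model shaped by chance. That needs some 10 to 20 independent variables tested at 5%, and the article states neither the number nor the test.

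**Conclusion.** The point holds in a limited form. In a 1:1 randomised trial, the stated rule admits covariates by observed imbalance, with no definition of imbalance and nothing elsewhere in the article to offset it. The model is therefore data-dependent and open to analyst choice, and balanced predictors are dropped. The supported cost is lost precision and a slightly conservative test.

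Under the assumptions above (60 independent observations per arm, one covariate, p<0.05 as the trigger), the power forgone against always adjusting is about 3 points at a correlation of 0.3 and 9 to 10 points at 0.5. The true size cannot be stated, because the sample size, the covariates and their correlations with the outcomes are not given. Partners within a couple are also unlikely to be independent, which the illustration ignores. This should be corrected, but it does not threaten the trial's validity.

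**What to change.** Replace the sentence with a short set of prognostic covariates, fixed before allocation and used whatever the baseline table shows. For example:

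- the enrolment score of the outcome being analysed;
- whether one or both partners were in the depression band at enrolment, which follows from the screening questionnaire;
- duration of infertility, if the infertility profile in Table 1 records it; the article names it only for the qualitative sampling.

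Include partner sex only in a model that accounts for the pairing of partners within couples, since it varies within the couple. Describe the arms at baseline without significance tests. Report any adjustment for an observed imbalance as a labelled sensitivity analysis, which keeps the wish to look at imbalance without letting it choose the main model.

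Always including the enrolment score also removes the conditional use of analysis of covariance in the same section, so one change of wording can settle both. The cost is that wording and a few degrees of freedom. If partner sex is included, the model for paired partners must also be specified.

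### A Kolmogorov-Smirnov gate can move the analysis to a Wilcoxon-type test that has no stated baseline adjustment and does not test the mean outcomes the trial defines

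*Protocol article*

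**What the plan says.** All analysis rules stand in one paragraph of the protocol article, Data management and analysis (third phase). The listed tests are the independent and paired t-tests, chi-square and repeated measures ANOVA. Three conditional rules follow.

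- **Baseline.** ANCOVA on the enrollment score is used only when the groups look different at enrollment: "If the measurements at the enrollment phase appear differently in the groups, analysis of covariance (ANCOVA".
- **Confounders.** Baseline values and "potential confounding variables which are different between the two groups will be adjusted".
- **Distribution.** "The data normality will be evaluated through the Kolmogorov-Smirnov test". Then: "If the data are not normally distributed, nonparametric tests such as Wilcoxon will be used".

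The paragraph does not say which data are tested (raw scores or residuals, pooled or by arm), at what threshold, or which Wilcoxon test is meant. It names no effect measure for the fallback.

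The Outcomes section defines the target in terms of means: "The outcome will be the mean score of depression, anxiety, stress, and infertility adjustment and the magnitude of their change". Data collection tools describes each DASS-21 subscale as seven items scored 0 to 3. Participants and setting admits "Couples, at least one of whom suffers from mild to moderate depression".

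**The concern.** The method of analysis would be chosen by a preliminary test on the trial's own data, and the two branches do not answer the same question.

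The parametric branch compares means and can be adjusted for the enrollment score. The fallback, read as a rank-sum test, compares distributions by rank, takes no covariate, and yields no mean difference with a confidence interval. If the groups differ at enrollment and normality is also rejected, the paragraph prescribes two things that cannot both be done with the named test: adjust for baseline, and use Wilcoxon.

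The gate also looks at the wrong thing if it is applied to raw scores. A linear model's normality assumption concerns its residuals, and matters only mildly at usual trial sizes. With a short bounded score, rejection becomes more likely as the sample grows, which is when the parametric method needs protection least.

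If the scores are skewed, the fallback could become the analysis that is actually reported.

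**Working it through.** **No figure to reproduce.** The protocol gives no sample size (it prints X), power, SD, effect or baseline/follow-up correlation. The only related input is a 95% confidence level, taken here as two-sided alpha 0.05. Correlation, effect, skewness and numbers per arm below are assumptions, so results are shown as ranges.

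**1. The rules side by side.**

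| Situation | Analysis the text leads to | Adjusted for baseline? | Tests the mean outcome? |
|---|---|---|---|
| Normal, groups alike at enrollment | t-test or RM ANOVA | t-test no; RM ANOVA not as a covariate | yes |
| Normal, groups differ at enrollment | ANCOVA | yes | yes |
| Not normal, groups alike | Wilcoxon or similar | no method stated | no |
| Not normal, groups differ | ANCOVA and Wilcoxon both called for | conflict | conflict |

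**2. Can the gate fire?** Seven items scored 0 to 3 give integers from 0 to 7 × 3 = 21. One partner may be free of depression, so low scores and right skew are plausible, though not stated. Rejection rates at the 5% level under two assumed shapes:

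| Assumed follow-up scores | Form of the test | 40 per arm | 60 per arm |
|---|---|---|---|
| Truncated negative binomial, control mean 6, SD 4.4, intervention mean 4.3 | uncorrected table | 7% | 23% |
| Same | corrected for estimated mean and SD (Lilliefors) | 73% | 90% |
| Rounded gamma, skewness about 1.4, both arms pooled | uncorrected table | 87–88% | 99% or more |

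The rates in the first two rows are of the size obtained when one arm is tested at a time. The method would therefore turn on details that the paragraph does not fix.

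**3. Power cost under normality.** Let k = 1.960 + z(power), the standardized effect at which ANCOVA has the stated power.

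- Unadjusted t-test: power = Φ(k·√(1 − ρ²) − 1.960).
- Rank-sum: power = Φ(k·√(1 − ρ²)·√0.955 − 1.960), where 0.955 is its efficiency under normality.

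Example with ANCOVA at 80% and ρ = 0.6: k = 1.960 + 0.842 = 2.802.

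- t-test: 2.802 × 0.8 = 2.241; Φ(0.281) = 61.1%.
- Rank-sum: 2.241 × 0.977 = 2.190; Φ(0.230) = 59.1%.
- Total loss: 80 − 59.1 = 20.9 points, of which 18.9 come from omitting the covariate and 2.0 from ranks.

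| ρ | t-test (ANCOVA 80%) | Rank-sum (ANCOVA 80%) | Loss, ANCOVA to rank-sum | Loss when ANCOVA has 90% |
|---|---|---|---|---|
| 0.3 | 76.2% | 74.3% | 5.7 | 4.4 |
| 0.4 | 72.8% | 70.9% | 9.1 | 7.3 |
| 0.5 | 67.9% | 65.9% | 14.1 | 11.7 |
| 0.6 | 61.1% | 59.1% | 20.9 | 18.3 |
| 0.7 | 51.6% | 49.8% | 30.2 | 28.1 |
| 0.8 | 39.0% | 37.6% | 42.4 | 42.4 |

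From t-test to rank-sum, the loss is 1.5 to 2.0 points throughout.

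**4. Power cost under skew.** Rounded gamma scores, 35% reduction in scale, 1,500 simulated trials per cell:

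| Per arm, ρ | ANCOVA | t-test | Rank-sum | t-test minus rank-sum |
|---|---|---|---|---|
| 40, 0.3 | 66.1% | 63.2% | 55.9% | 7.3 |
| 40, 0.5 | 72.0% | 63.9% | 56.3% | 7.6 |
| 40, 0.6 | 78.8% | 61.1% | 53.3% | 7.8 |
| 40, 0.7 | 87.1% | 61.7% | 52.5% | 9.2 |
| 60, 0.3 | 83.3% | 80.7% | 74.4% | 6.3 |
| 60, 0.5 | 90.1% | 81.1% | 74.3% | 6.8 |
| 60, 0.6 | 92.5% | 80.7% | 72.8% | 7.9 |
| 60, 0.7 | 96.5% | 79.7% | 72.4% | 7.3 |

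From ANCOVA to rank-sum the loss runs from 83.3 − 74.4 = 8.9 to 87.1 − 52.5 = 34.6 points. Omitting the covariate is the larger part from ρ = 0.5 upward. At ρ = 0.3 the change to ranks is the larger part (7.3 of 10.2 points at 40 per arm).

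**5. Does ANCOVA need the protection?** With the truncated negative binomial scores and independent individuals, its type I error was 5.6% (40 per arm) and 4.1% (60 per arm), against a nominal 5%.

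**The case against.** **The power loss belongs mainly to another choice.** A reader might infer that the gate costs about 20 points of power. The protocol does not support that. The figure needs an assumed correlation near 0.6 and ANCOVA as the standing comparator, whereas here ANCOVA is used only if the groups look different at enrollment. In a balanced trial the fallback replaces an unadjusted t-test or RM ANOVA, and against the t-test it costs 2 to 9 points. This objection stands.

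**Couples.** A reader might also infer that Wilcoxon discards the couple structure. No listed test is said to include it. With partners treated as independent (40 couples per arm), simulated type I error was 8.2% for the t-test and 7.9% for the rank-sum at an intra-couple correlation of 0.3, and 10.6% and 10.7% at 0.5. Ranks are no worse; the missing couple term is a separate issue.

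**Baseline and effect size remain available.** A rank test on change scores uses the baseline, a rank-based shift estimate exists, and means can be reported beside any test. True, but none of this is stated. In the skewed simulation a rank-sum test on changes had 40–70% power at 40 per arm and 54–86% at 60, against 66–87% and 83–97% for ANCOVA.

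**Within-arm test.** Wilcoxon could mean the paired signed-rank test, which would not compare the arms. Since Sampling and data collection and Outcomes both call for comparison between groups, a purely within-arm reading is unlikely, and a condensed article may leave the exact test to the analysis plan.

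**Skew is assumed.** The protocol gives only the score range and the entry rule. This limits what can be said about how often the gate fires. It does not remove the conflict between the rules.

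**Conclusion.** The point holds as a poorly fixed rule, not as missing detail. Followed as written, the normality gate can remove the baseline and confounder adjustment promised just before it, and can replace a test of the stated mean outcomes with one that does not address them. That conclusion rests on the text alone.

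Its size does not. How often the gate fires (7% to over 99%) depends on score shape, sample size and the form of the Kolmogorov-Smirnov test. The power cost is about 2 to 9 points against the default t-test, and about 4 to 42 points against ANCOVA for correlations of 0.3 to 0.8. Most of the latter comes from omitting the enrollment score, except under skew with a low correlation. No single figure should be quoted as the cost. The change is worth making before data are seen, but the trial does not fail without it.

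**What to change.** 1. Delete the Kolmogorov-Smirnov rule and the switch that follows it.
2. Specify one between-group analysis of the 3-month score, adjusted for the enrollment score by ANCOVA or a mixed model, to be used whatever a normality test or a baseline comparison shows. The protocol has no such unconditional analysis at present, so it has to be written in.
3. Report the adjusted mean difference with a confidence interval. Judge residuals rather than raw scores, and use robust or bootstrap intervals if they look poor.
4. Keep any rank analysis as a sensitivity analysis, named as the between-group rank-sum test, with the values it is applied to.
5. Include the couple in the specified model, resampling or clustering by couple for robust or bootstrap intervals. This also meets the separate issue that no listed test accounts for couples.

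Cost: analysis wording only. Recruitment already has the questionnaires completed at the first interview, so no new measurement is needed.
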